#### Waiting list group

2.12.4

No intervention will be performed in this group. The participants are required to continue their current living habits, including exercise and diet, while receiving free ophthalmologic examinations throughout the full observational period. To meet the requirements of the Rule of Ethics, all participants in the waiting list group will be offered free acupuncture treatment of their choice at the completion of the study.

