## Introduction

1

Myopia is the most common cause of avoidable visual impairment worldwide.^[1,2]^ Young academics in South-East Asia now face a frequency of up to 95.5% of myopia,^[3]^ accompanied by a high prevalence of high myopia (10–20%).^[4]^ In 2000, there were 1406 million myopia patients and 163 million high myopia patients, and it is predicted that by 2050, there will be 4758 million myopia patients (49.8% of the world population).^[5]^ Myopia brings further vision challenges, as high myopia increases the risk of pathologic ocular changes such as cataract, glaucoma, retinal detachment, myopic macular degeneration, and myopic choroidal neovascularization, all of which can cause irreversible vision loss.^[6,7]^ The global potential productivity loss associated with the burden of vision impairment was estimated at US$244 billion from uncorrected myopia and US$6 billion from myopic macular degeneration.^[8]^

The multifactorial mechanism of the increased prevalence of myopia is not fully understood. Several theories have been proposed to explain the recent increase and its earlier onset in children, including genetic markers,^[9,10]^ increased near work,^[11]^ and less time spent outdoors.^[12,13]^ There has been an increase in efforts to slow the progression of myopia, and a variety of treatment methods have been recommended for the management of myopia. Conventional therapies included single vision spectacle lenses, multifocal eyeglasses, novel lens eyeglasses, various contact lens therapies, orthokeratology, and muscarinic antagonists such as atropine and pirenzepine.^[14,15]^ However, it is reported that none of the spectacle lenses had any significant effect in slowing the progression of myopia. Gas permeable contact lenses have been shown to slow the progression of myopia, but the low incidence of microbial keratitis should not be dismissed, especially in children. The pharmacological treatment has been reported to be associated with adverse effects, including pupil dilation and temporary paralysis of accommodation.^[16–19]^ Consequently, this reality drives us to search for additional effective and low-risk interventions of treatment for myopia.

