### Study design

2.2

This clinical study is a parallel-group, randomized controlled, and single-blind study. The experiment will begin in August 2020 and will be completed in August 2023. After obtaining informed consent, 300 eligible adolescents will be recruited and randomly divided into acupuncture Deqi group, acupuncture without Deqi group, and waiting list group. The trial will include a 3-month treatment period and a 9-month follow-up period. All groups will be given frame glasses for corrective treatment; patients in the acupuncture Deqi group will also be treated with acupuncture at acupoints around the eyes to Deqi, while acupuncture without Deqi group will be treated with acupuncture, but no needle manipulation will be performed. The waiting list group will not receive acupuncture treatment. Results will be assessed at 3 points, including baseline, end of acupuncture treatment, and end of follow-up (Fig. 1 flowchart and Fig. 2 visit indicators). The purpose of this study is to objectively evaluate the clinical efficacy of acupuncture at 3 acupoints (Sizhukong, Tongziliao, and Sibai) in adolescents with myopia. All patients will be required to complete written informed consent before enrolment. If patients are unable to complete written informed consent, it will be obtained from their relatives.

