#### Basic treatment

2.12.1

The basic treatment includes conventional frame glasses correction treatment. All patients will receive disease health education, including eye hygiene, eye use time, rest time, and health consultation, but in order to avoid the confounding effect of excessive eye use, the research team will not provide special eye health intervention measures.

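### The waiting-list section says no intervention and tells that arm alone to keep its habits, which conflicts with the glasses and eye-use education promised to every participant

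*Protocol article*

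**What the plan says.** Glasses are described as common to all arms. The Abstract and section 2.2 (Study design) both state: "All groups will be given frame glasses for corrective treatment". Section 2.12.1 (Basic treatment) repeats this, "The basic treatment includes conventional frame glasses correction treatment", and adds education for everyone: "All patients will receive disease health education, including eye hygiene, eye use time, rest time, and health consultation". It then says that "the research team will not provide special eye health intervention measures". The legend of Figure 1 also defines basic treatment as glasses plus health education.

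Section 2.2 names only one thing that the third arm goes without: "The waiting list group will not receive acupuncture treatment".

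Section 2.12.4 (Waiting list group) uses different terms: "No intervention will be performed in this group. The participants are required to continue their current living habits, including exercise and diet". The only thing it lists as provided during observation is free eye examinations. It mentions neither glasses nor education.

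Section 2.16 plans a mixed-model test of acupuncture without Deqi against waiting list, and the Discussion interprets that contrast as the nonspecific effect.

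**The concern.** The waiting-list section raises two separate problems.

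The first is scope. Section 2.12 is headed Intervention, and its first subsection is the basic treatment. Section 2.12.4 stands under the same heading, so "No intervention will be performed in this group" literally covers the glasses and education that other sections promise to all.

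The second is the instruction on habits. It appears for this arm only; sections 2.12.2 and 2.12.3 give the needled arms nothing similar. Education on eye use and rest has a purpose only if it can change what a child does. A waiting-list child is therefore taught about eye use and also required to carry on as before, while a needled child gets the teaching without that requirement.

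Habits matter for this outcome on the protocol's own account. The Introduction lists more near work and "less time spent outdoors" among the proposed explanations for rising myopia. At stake is whether the contrast between acupuncture without Deqi and waiting list can be read as the effect of being needled, rather than that effect mixed with a different behavioural instruction.

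**Working it through.** The protocol gives no figure for this point, so the check is a comparison of the text by arm.

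1. **Glasses.**
   - Deqi arm: yes (Abstract, 2.2, 2.12.1, restated in 2.12.2).
   - Without-Deqi arm: yes (Abstract, 2.2, 2.12.1, carried over by the statement in 2.12.3 that other procedures are unchanged).
   - Waiting list: yes by the Abstract, 2.2 and 2.12.1; no by the literal wording of 2.12.4.
2. **Education on eye use and rest.**
   - Both needled arms: yes (2.12.1).
   - Waiting list: yes by 2.12.1; no by the literal wording of 2.12.4.
3. **Instruction to keep usual habits.**
   - Both needled arms: none stated.
   - Waiting list: yes (2.12.4).
4. **Needling.**
   - Both needled arms: yes.
   - Waiting list: no (Abstract, 2.2).

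On rows 1 and 2, several statements outweigh one, and section 2.2 and the Discussion describe the missing element as acupuncture. The most plausible plan is the same glasses and education in all arms, so these rows show an inconsistency in the text and not a planned difference.

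Row 3 does not go away on that reading. Even if the no-intervention sentence means no acupuncture, the habit instruction remains in one arm only. Exercise and diet are given as examples and do not by themselves limit the instruction, so eye use and rest are not clearly outside it. Blinding does not offset this, because a child who is never needled can tell.

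**Which analyses are touched.** At 1:1:1 allocation of 300, the waiting list has 300/3 = 100 participants. Section 2.16 names two mixed-model contrasts. Deqi against no Deqi does not use this arm. No Deqi against waiting list does, and so does the three-group repeated-measures ANOVA.

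**Size.** The documents give no effect of education or habits on diopter. The only difference available is in section 2.9: 1.81 − 1.52 = 0.29 D. It is stated for experimental group 1 against experimental group 2 and is not presented as a waiting-list difference, so it is no yardstick here.

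**The case against.** The strongest reply is that this is loose drafting. Section 2.12.4 follows the basic treatment and the two needled arms, so no intervention naturally means nothing on top of the basic treatment. A site would have to ignore several explicit statements to withhold glasses. The without-Deqi section does not restate glasses or education either, and nobody infers that they are withdrawn there. The habit instruction mentions exercise and diet, not near work or time outdoors, and silence about habits in the needled arms of a condensed article is not permission to change them.

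Much of this stands. A reader might infer that the trial compares glasses and education in the needled arms with neither in the waiting list, so that the contrast is confounded by design. The documents do not support that, because they promise both to everyone. A reader might also see a contradiction within section 2.12.1, but general education can coexist with withholding special measures. Nor does any text say that education is repeated at needling sessions. Extra staff contact there belongs to the nonspecific effect that the Discussion sets out to measure.

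The reply does not explain why one arm alone is told to keep its habits, or how that fits with teaching the same children about eye use and rest.

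**Conclusion.** The point holds in a limited form. Section 2.12.4 is inconsistent with the Abstract and sections 2.2 and 2.12.1. It also places on one arm a behavioural instruction that conflicts with education meant for all. This leaves a possible difference other than needling in the contrast of acupuncture without Deqi against waiting list. It does not affect Deqi against no Deqi.

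It is tempting to go further and say that the bias favours needling by some stated amount. The text gives no basis for that. The direction depends on whether the education changes behaviour, whether families read the instruction as covering eye use, and whether they follow it; the documents report none of these.

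The conclusion rests on two readings: that shared basic treatment is intended, and that the habit instruction is confined to this arm because it appears nowhere else in the article. If the full protocol gives it to all arms, the between-arm difference disappears and only the conflict with the education remains.

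**What to change.** Reconcile section 2.12.4 with the Abstract and sections 2.2 and 2.12.1. State that the waiting-list arm receives no acupuncture and the same basic treatment (section 2.12.1) as the other two arms. Then either delete the instruction on living habits or move it to section 2.12.1 so that all three arms receive it in identical words, phrased so that it does not contradict the education on eye use and rest.

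The cost is a few sentences of protocol wording and matching participant information. No extra participants, visits or measurements are needed, and the analysis does not change. If children have already been enrolled, record what the waiting-list families were actually given and told, so that the contrast can be interpreted.

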#### Primary outcome

2.12.5

The primary outcome will be diopter measurement of the patients before treatment, 1, 2, 3 months after treatment, and follow-up for 6 , 9 , and 12 months.

Full cycloplegia was obtained 45 minutes after administration of 1% cyclopentolate eye drops (15 mL; Alcon-Couvreur, Puurs, Belgium); Subsequently, the objective optometry (computer optometry and retinoscopy) was measured with a Topcon auto refractor KR8900 (Topcon, Tokyo, Japan); and then subjective optometrics. Subjective optometrics will be divided into the following 2 parts: optometrics will be conducted on a single eye (the right eye followed by the left eye), and a bilateral eye balance examination. Subjective optometrics of a single eye will be divided into the following 3 stages: the initial maximum plus the maximum visual acuity (MPMVA) will be identified, Jackson cross cylindrical lenses will be used to determine the axial direction and degree of the cylindrical lens, and the MPMVA will be repeated. The results will be recorded after optometrics. When the pupils recover, a re-examination will be carried out (3 days after the use of cyclopentolate hydrochloride eye drops). After re-examination, the glasses will be tried again. The degree of the glasses will be marked on the glass trial frame, to be chosen by the subjects based on subjective judgment. Finally, the diopter of the glasses and prescription glasses will be determined. The optometrist will not participate in other parts of the trial.

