**Discussion::**

Our study will compare acupuncture Deqi with acupuncture without Deqi, and place it in a control group for the treatment of myopia. The results of this trial are expected to provide solid evidence for the effectiveness and safety of acupuncture combined with Deqi in the treatment of myopia, and hope to provide a reference for clinical practice. The primary outcome will be diopter measurement of the patients before treatment.

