### Sample size

2.9

This study is a RCT, and the diopter of the research object is the main observed outcome index. According to previous literature reports, it is estimated that the mean diopter of experimental group 1 is -1.52, the standard deviation is 0.87, and the diopter of experimental group 2 is- 1.81, the standard deviation is 1.25. Set α = 0.25 (2-sided) and β = 0.10. We use PASS 15 software (PASS 15.0.5 NCSS, LLC USA) to calculate the experimental size of the test group and the control group N1 = N2 = N3 = 74 cases. Assuming that the loss to follow-up rate of the study subjects is 20%, the sample size is N1 = N2 =  = N3 = 74÷0.8 = 93 cases. Therefore, the minimum sample size included in this study is 279 cases. In the actual study, a total of 300 cases will be included.

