### Data management and quality control

2.15

All participants are assessed at the first, second, third, sixth, ninth, and twelfth months after recruitment. A well-trained assessor, who is blinded to the treatment assignment, will collect clinical data using CRF files at each visit. Another 2 pre-trained data managers will verify and cross-check the CRFs, for the sake of ensuring reliability and accuracy of the data. If there are any queries in the CRFs, the results will be sent to the third investigator for resolution. Data managers will also be responsible for administration, coordination, and monitoring (including Excel spread sheet-set up, data entry, coding, and query management). Any incomplete data will be coded as unknown, missing, or not applicable, and all data will be anonymously extracted to keep the identities of patients confidential. Results of the analysis must not be released with individual identification of the subject until the Excel spread sheet is closed.

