### Statistical analyses

2.16

Data analyses will be processed with SPSS 22.0 (SPSS Inc., Chicago, IL) and supervised by a skilled statistician blinded to group allocation.

The Full Analysis Set (FAS) is for all participants who have been randomized in terms of the intention-to-treat (ITT), and the per-protocol analysis set (PPS) and is for the individuals who complete the trial and do not have significant protocol violations. On the basis of rule of the last-observation-carried-forward, missing values will be imputed. In order to evaluate therapeutic effect and safety, the FAS and PPS will be used simultaneously.

Categorical data, such as gender and medical history, will be tabulated with frequencies or percentages; and continuous data, such as age and disease course, will be reported as mean ± standard deviation (SD), or median. For the baseline variables, sociodemographic data and other basic indicators will be carried out using analysis of variance (ANOVA) and χ^2^. To compare variables before and after treatment in the same group, a paired *t* test will be used. Repeated-measures ANOVA will be used to compare the intergroup differences among the 3 groups. Tests of ITT between the acupuncture with the deqi group and acupuncture without the deqi group arms and between the acupuncture withou the deqi group and waiting-list group arms with respect to the change will based on time-intervention interactions in the mixed-effect models. A *P* value of less than .05 (2-sided) indicates a statistically significant difference, with 95% confidence intervals.

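### The primary outcome covers six post-baseline visits with no deciding visit or contrast, the sections disagree on visits and clock, and the whole-course tests do not separate end-of-treatment benefit from persistence

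*Protocol article*

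**What the plan says.** Section 2.12.5 (Primary outcome) gives the primary outcome as "diopter measurement of the patients before treatment, 1, 2, 3 months after treatment, and follow-up for 6 , 9 , and 12 months". That is baseline plus six later visits, with no visit marked as primary and no change score or summary measure. The Discussion paragraph of the Abstract shortens this to "The primary outcome will be diopter measurement of the patients before treatment", which on its own names only the baseline value.

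Section 2.2 (Study design) describes a different schedule: "Results will be assessed at 3 points, including baseline, end of acupuncture treatment, and end of follow-up". It also sets the periods: "The trial will include a 3-month treatment period and a 9-month follow-up period".

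Section 2.15 (Data management and quality control) counts from another origin: "All participants are assessed at the first, second, third, sixth, ninth, and twelfth months after recruitment".

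Section 2.16 (Statistical analyses) gives two between-group analyses. The first reads: "Repeated-measures ANOVA will be used to compare the intergroup differences among the 3 groups". The second compares Deqi with non-Deqi acupuncture, and non-Deqi acupuncture with the waiting list, "with respect to the change will based on time-intervention interactions in the mixed-effect models". Neither sentence names a visit, a period or the coding of time.

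Section 2.9 (Sample size) plans on values such as "the mean diopter of experimental group 1 is -1.52, the standard deviation is 0.87", with no visit attached.

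**The concern.** Needling stops after 3 months and the next 9 are untreated. Whether diopter differs at the end of needling, and whether a difference lasts to the end of follow-up, are separate questions that can have opposite answers. A test over the whole course answers neither by itself. Because nothing in the article says which visit or contrast decides, a reader of the final report could not tell whether the result presented as primary was chosen before or after the data were seen. The sections also disagree on how many assessments there are and when the clock starts, so the plan cannot be used to settle the matter afterwards.

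**Working it through.** The plan states no figure for this point. The check is therefore a comparison of the sections, followed by two illustrations that each rest on a stated assumption.

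**Number of assessments.** Section 2.12.5 lists months 1, 2, 3, 6, 9 and 12, which is six post-baseline visits. Section 2.15 lists the same six. Section 2.2 has three points including baseline, so two post-baseline.

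**Clock.** Section 2.2 gives 3 + 9 = 12 months in total. Counted from recruitment, months 1, 2 and 3 fall inside the treatment period. Counted literally from the end of treatment, they fall at 3 + 1 = 4, 3 + 2 = 5 and 3 + 3 = 6 months. If month 12 were counted that way too, it would fall at 3 + 12 = 15, outside the 12-month trial.

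**Illustration 1: one slope over the course.** Assumption: time is linear, each group has its own intercept, and visits are weighted equally. Inputs are t = 0, 1, 2, 3, 6, 9, 12 (months from the start) and an assumed group difference d(t) that rises in a straight line from 0 to a 1-unit benefit at month 3.

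- Sum of t = 33 and sum of t² = 275, so Sxx = 275 − 33²/7 = 119.43.
- *Benefit held to month 12:* d = 0, 1/3, 2/3, 1, 1, 1, 1. Sum of d = 5 and sum of t·d = 31.67. Slope = (31.67 − 33 × 5/7)/119.43 = 8.095/119.43 = +0.0678 per month. Over 12 months: +0.81.
- *Benefit fading to 0 at month 12:* d = 0, 1/3, 2/3, 1, 2/3, 1/3, 0. Sum of d = 3 and sum of t·d = 11.67. Slope = (11.67 − 33 × 3/7)/119.43 = −2.476/119.43 = −0.0207 per month. Over 12 months: −0.25.

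These are changes implied by the slope, not fitted differences at a visit. The fitted intercepts are 0.395 (held) and 0.526 (fading), so in the fading case the fitted difference at month 12 is 0.526 − 0.249 = +0.28.

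If the groups share a common baseline (line through the origin), the fading slope is 11.67/275 = +0.042 per month and the negative sign is gone.

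**Illustration 2: any visit counts.** Assumption: each of six visits is tested at two-sided 0.05 and one significant visit is enough. With independent tests, 1 − 0.95⁶ = 0.265. With equal between-visit correlation (simulated, 400,000 draws, threshold 1.96), the chance is 0.14 at correlation 0.8 and 0.11 at 0.9. The article gives no between-visit correlation, so these values are assumed. Repeated refraction in the same child is likely to be strongly correlated, so the lower figures are the more relevant.

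**The case against.** Several points on the other side stand.

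- *Time coding.* Section 2.16 does not say that time is linear, and the repeated-measures ANOVA it also names normally treats time as a factor. With time as a factor, the interaction is a joint test without a sign, and a month-3 benefit that later fades contributes to it. A reader might infer that the planned test would give the wrong sign for a fading benefit. The article does not support that: the sign needs linear time and a free intercept per group.
- *Error rate.* A reader might infer a false-positive rate of 26%. The article announces no between-group tests at single visits, and independence is implausible here.
- *Clock.* A reader might infer that the first three visits really take place at months 4 to 6. More probably the wording is loose for months from the start of treatment. The 12-month total, the schedule in section 2.15 and the safety schedule in section 2.14 (which runs from before treatment through months 1 and 2 to the end of treatment) all point that way.
- *Detail elsewhere.* Time coding is often left to the analysis plan, and the two figures cited for the visits are not shown.

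The core is untouched. The article does not merely omit the schedule; it states it in conflicting ways. Treating time as a factor does not cure the problem either, because a joint test over all visits still does not say whether benefit arose during needling or lasted afterwards. Only a named contrast does that, and none is named.

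**Conclusion.** The point holds in this form: the primary outcome has no deciding visit or contrast, section 2.2 conflicts with sections 2.12.5 and 2.15 on the number of assessments, and the time origin is worded in two ways that must be reconciled. The stated tests span treated and untreated months without separating them. This part rests on the text alone.

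The numbers show what is at stake and are not properties of the plan. Under linear time with free intercepts, the same month-3 benefit gives a slope-implied 12-month change anywhere from +0.81 to −0.25 units between the two patterns tried. Under selection among six visit-level tests, the false-positive chance per contrast is about 11% to 14% at correlations of 0.9 to 0.8, with 26% as the independent-tests extreme. The two figures belong to different analyses and should not be combined.

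Nor do the documents rank month 3 above month 12. Preferring month 3 is a judgement, because it is the end of the treatment under test.

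**What to change.** 1. Bring sections 2.2, 2.12.5 and 2.15 to one visit list and one clock, in months from randomisation, and correct the shortened sentence in the Abstract.
2. Name one primary time point from the two post-baseline points already in section 2.2. Month 3, the end of treatment, is the natural choice; month 12 is acceptable if justified in advance. Make the other the key secondary time point, and the remaining visits supportive.
3. In the mixed model, enter visit as a category and take the between-group contrast in change in diopter from baseline at the named visit. State that this contrast, and not the overall interaction or the repeated-measures ANOVA, decides the primary question.

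No new visits or data are needed. The sponsor gives up claiming success at other visits, and must state which visit the planning values in section 2.9 refer to. If they do not describe the visit chosen, the sample size has to be justified again for that visit.
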